#### Physical or Visual Causes of Noncompletion

If the suspected reason for non–self-completion is physical or visual impairment, then the participant is to be provided assistance to complete the PROMs, cognitive screen, and anxiety and depression screen. The administrator should read the question and note down the response. However, there should be no deviation from the wording of the questions or response options. Potential physical or visual deficits that could be expected are as follows: hemiparesis, hemiplegia, hemi-inattention, and hemianopia.

During Periods B and C, if the participant is unable to complete the PROM, cognitive screen, or anxiety and depression screening questions via telephone, a decision about whether a suitable alternative follow-up method is appropriate should be made. This is to be based on clinical judgment, provided the participant still wishes to continue in the study.

During collection of data, the use of secondary sources to aid data collection is permitted for the following; demographic, clinical, lifestyle, poststroke sequelae and functional assessments. The participant’s family, friends, care team, or medical notes are permissible sources of consultation. However, secondary sources are not permitted to aid the completion of the patient-reported data such as cognitive screen, PROM, or anxiety and depression screen.

### Data Analysis

The objective of this study is to estimate the prevalence of morbidity at 6 months with a 95% CI width of ±5%.

The study will be deemed to have ended following the collection of data for Period C from the last participant registered in the study. All participants recruited in the study will be included in the analysis population. All clinical characteristics will be presented in a descriptive narrative.

#### Morbidity Prediction

Baseline clinical and patient demographic variables will be used to predict the mediating effects of a patient exhibiting poststroke morbidity.

Continuous outcomes are analyzed using a mixed-effects linear model, and binary outcomes are analyzed using logistic regression. All estimates will be presented with 95% CI. Sites will be fitted by a random intercept model. For outcomes that analyze at a single time point, we will fit a single random intercept of patients nested within the site using a random intercept model. Moreover, we will be fitting a three-tier multilevel model, including two random intercepts. Multiple patient time points will be fitted within a patient, and the patient will be fitted within a site. Statistical analysis will be performed using Stata Statistical software (StataCorp LLC).

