**Methods:**

A total of 500 participants will be recruited across Wales and England within 14 days following an admission to a stroke unit for either an ischemic or hemorrhagic stroke as part of a multicenter cohort study. Participants are assessed at baseline ≤14 days poststroke and subsequently at 90 (± 14) days and 180 (± 14) days poststroke. At each time point, data will be collected relating to the following domains: participant demographics, routine clinical, patient reported, cognitive status, emotional well-being, and functional ability.

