### Aims and Objectives

This paper describes the protocol for the Morbidity Prevalence Estimate at 6 Months Following a Stroke (MORe PREcISE) study (ClinicalTrials.gov NCT03605381—Registered: 30/07/19). The primary objective is to determine the prevalence of morbidity at 6 months secondary to a stroke, predictors of morbidity, trends in health-related quality of life (HRQoL), and function. The definition of morbidity secondary to stroke includes the following: aphasia, anxiety, depression, dysarthria, dysphagia, hemianopia, hemiparesis, hemiplegia, hemi-inattention, cognitive impairment, and functional impairment including activities of daily living and social interaction or roles.

Therefore, this study will collect a wide range of data related to the most common morbidity secondary to stroke, from stroke onset to 6 months poststroke across England and Wales. The secondary objectives include describing trends in domains such as HRQoL from acute onset to 6 months poststroke. It will also explore trends in pre- and poststroke functional levels, as assessed by the Modified Rankin Scale (mRS) [9] from the prestroke period to 6 months poststroke. Lastly, trends in outcomes (patient reported, functional, treatment, and process of care) by geographical distribution, such as country, health board/trust, local authority, and hospital (research site) coverage, will be explored.

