#### Sample Size

In order to estimate the prevalence of stroke morbidity at 6 months, assuming a 35% morbidity rate, with a 95% CI width of ±5%, will require 350 stroke survivors. Assuming that there is a 30% dropout [11] at the 6-month visit, the aim is to recruit a minimum of 500 stroke survivors. This will be achieved by aiming to approach all appropriate inpatients fulfilling the eligibility criteria across the 20 sites. Stata Statistical software will be used for the analyses.

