### Data Collection

Following enrolment into the study, data collection is divided into three distinct periods: Period A (within 14 days from the onset of stroke), Period B (90 days poststroke ± 14 days), and Period C (180 days poststroke ± 14 days) as per the participant flow diagram (Figure 1). A standardized SPIRIT (Standard Protocol Items: Recommendations for Interventional Trials) [20] schedule of assessments is presented in Figure 2.

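### The only stated repeated-measures model, two random intercepts, implies equal correlation between the acute, 90-day and 180-day visits and can misstate the precision of change estimates for continuous outcomes

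*Protocol article*

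**What the plan says.** The Morbidity Prediction section under Data Analysis in the protocol article names the outcome models: "Continuous outcomes are analyzed using a mixed-effects linear model, and binary outcomes are analyzed using logistic regression". It gives a simpler random-intercept model for outcomes analysed at a single time point. For repeated outcomes it says "we will be fitting a three-tier multilevel model, including two random intercepts", and gives the nesting: "Multiple patient time points will be fitted within a patient, and the patient will be fitted within a site". It adds: "All estimates will be presented with 95% CI". It names no random slope, serial correlation, residual covariance or robust variance, and no other repeated-measures model appears in the article.

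The Abstract gives the visit times: "Participants are assessed at baseline ≤14 days poststroke and subsequently at 90 (± 14) days and 180 (± 14) days poststroke". Period A is collected around the stroke admission. Period B is by telephone or face to face, mostly with people back in the community, and the Period C section says that its procedure repeats Period B exactly.

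Aims and Objectives sets the trend objective: "The secondary objectives include describing trends in domains such as HRQoL from acute onset to 6 months poststroke". The Sample Size section plans for loss: "Assuming that there is a 30% dropout" at the 6-month visit.

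**The concern.** A patient intercept adds the same quantity to all of a patient's values, and a site intercept does the same for all patients at a site. If what remains is independent between visits, each visit has the same variance and each pair of visits the same correlation. The model therefore treats the step from acute admission to 6 months as no more variable between patients than the step from 3 to 6 months.

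The design points the other way. Two follow-ups under one procedure, about 90 days apart, should agree with each other more than either agrees with an assessment made in the first two weeks. If so, the common correlation is too high for the pair spanning onset to 6 months and too low for the two follow-ups. The interval for the change named in the trend objective would then be falsely precise. The interval for late change, where a plateau or decline would show, would be needlessly wide. A larger sample does not help, because the ratio of model to true standard error does not depend on the number of patients.

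A second, lesser effect is that a likelihood fit uses the assumed correlation to allow for patients who leave. A wrong correlation can therefore shift the 6-month mean when leaving depends on earlier scores.

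**Working it through.** **The plan's own figure.** With prevalence 0.35 and half-width 0.05, n = 1.96² × 0.35 × 0.65 / 0.05² = 349.6, so 350, and 350 / 0.70 = 500. Both stated figures reproduce. Neither uses the repeated-measures model.

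**Inputs.** The model structure, the three visits and the 30% dropout come from the article. It gives no between-visit correlations or SDs, so those below are assumptions, shown as a range. The first check takes complete data, visit as a categorical effect and, in the table, equal SDs. Site variance is ignored; a site intercept cancels from a within-patient change.

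**Formulas.** For visits j and k with common SD s and n patients, the true variance of the mean change is 2s²(1 − r_jk)/n. Fitted to such data, the two-intercept model settles on the average correlation r̄ and reports 2s²(1 − r̄)/n. Hence:

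- SE ratio (model / true) = √[(1 − r̄)/(1 − r_jk)]
- coverage of a nominal 95% interval = 2Φ(1.96 × SE ratio) − 1

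**Worked case.** Correlations 0.50 (0–90 days), 0.40 (0–180) and 0.75 (90–180) give r̄ = 1.65/3 = 0.55.

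- Baseline to 6 months: √(0.45/0.60) = 0.87, coverage 91.0%
- 3 to 6 months: √(0.45/0.25) = 1.34, coverage 99.1%

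**Range.**

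| Assumed correlations (0–90 / 0–180 / 90–180) | r̄ | SE ratio 0–180 (coverage) | SE ratio 90–180 (coverage) |
|---|---|---|---|
| 0.60 / 0.60 / 0.60 | 0.60 | 1.00 (95.0%) | 1.00 (95.0%) |
| 0.50 / 0.45 / 0.65 | 0.53 | 0.92 (92.9%) | 1.15 (97.6%) |
| 0.50 / 0.40 / 0.75 | 0.55 | 0.87 (91.0%) | 1.34 (99.1%) |
| 0.40 / 0.30 / 0.80 | 0.50 | 0.85 (90.2%) | 1.58 (99.8%) |

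With the third row's correlations and a baseline SD 20% smaller, the ratios are 0.88 (91.7%) and 1.25 (98.6%).

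**Dropout.** Both covariance models were fitted by maximum likelihood to 400,000 simulated patients per scenario. Loss was 15% by 90 days and 30% by 180 days. Its chance depended on the last observed value, with a log-odds slope of 0.5 or 1.0 per unit of outcome (one SD, except at baseline in the unequal-SD case). Absolute bias in the 180-day mean:

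- two-intercept model, unequal correlations and equal SDs: 0.006 to 0.029 SD
- two-intercept model, baseline SD also 20% smaller: 0.020 to 0.039 SD
- unstructured covariance: within 0.003 SD throughout
- simple mean of completers: 0.09 to 0.17 SD

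For scale, the true SE of the baseline-to-180-day change with 350 patients in the worked case is √[2 × 0.60/350] = 0.059 SD.

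**The case against.** The strongest reply is that the article fixes only the random intercepts. A residual structure or a robust variance can be set alongside them in Stata, and such detail may stand in the full protocol or analysis plan, neither of which is shown. That limits the claim: a reader might infer that the article forces equal correlation, and it does not. It implies it if residuals are independent, the usual reading of a random-intercept model. The point stands because the article states a structure, and that structure as written is restrictive; it does not rest on silence.

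Second, the sentence sits under Morbidity Prediction, and the trend objectives speak only of describing and exploring. The link to those objectives is inferred. It is reasonable, since no other repeated-measures model is given and all estimates are to carry 95% intervals, but it remains an inference.

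Third, a reader might infer serious dropout bias from 30% loss. The check does not support that: the bias is below one standard error, and the stated model removes most of the bias of completer means. The Missing Outcome Data section also provides for exploring patterns and possibly imputing when more than 5% is missing, which 30% would exceed. Imputation would not by itself correct the standard errors. The check also treats all loss as dependent on the last observed score, whereas the 60-day and 150-day procedures withdraw participants after a further stroke or palliative status, and some will die.

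Fourth, the figures cover continuous outcomes only. Binary outcomes were not computed, and the modified Rankin Scale is ordinal.

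**Conclusion.** The point holds in conditional form. As written, and with independent residuals, the model treats the acute, 90-day and 180-day visits as exchangeable. If the follow-ups correlate at 0.65 to 0.80 with each other and at 0.3 to 0.5 with baseline, standard errors for baseline-to-6-month change in continuous outcomes are about 8 to 15% too small, and those for 3-to-6-month change about 15 to 58% too large. These correlations are assumptions, and with equal correlations and variances the error is nil. The design makes equality implausible but does not disprove it.

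It would go too far to say that the intervals will be wrong, or that the headline result is at risk. The article lacks the correlations needed for the first, and the 6-month prevalence does not use this model. This is a worthwhile correction to secondary analyses of continuous outcomes over time.

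**What to change.** For continuous outcomes analysed over the three visits, keep the site random intercept and replace the patient intercept with an unstructured 3×3 within-patient residual covariance by visit. In Stata's mixed command this is the residuals(unstructured, t(visit)) option at patient level, with the patient constant suppressed. State that the two-intercept model will be used only if this fit does not converge.

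Do not rely on cluster-robust standard errors as the remedy. With a site intercept the clusters would be the 20 sites, which is few for that estimator, and robust standard errors would leave any dropout bias in place.

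The cost is one sentence and four more covariance parameters: six within-patient (three variances, three covariances) against two (patient and residual variance). That is negligible with about 500 patients (536 recruited, according to the Results section) at three scheduled visits. If the visits are in fact exchangeable, almost nothing is lost.

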#### Psychometric Analysis

The patient-reported outcomes will be assessed for the following psychometric properties: validity (content validity and convergent validity) and reliability (internal consistency).

#### Missing Outcome Data

Due to the nature of our data collection methods, and evidence from previous studies of this nature, we anticipate negligible missing instrument levels, and in this case, a complete case analysis will be carried out. If the level of missing outcome data is not considered negligible (>5%), missing data will be explored for patterns of missingness and may be imputed using appropriate methods. Imputation methods will depend on the proportion of missingness and reason for the missing data.

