**Conclusions:**

The primary outcome is the prevalence of morbidity at 6 months secondary to a stroke. Further analysis will consider temporal changes in the health-related domains to describe trends among baseline, 3-, and 6-month time points.

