#### Period B—90 Days Poststroke (± 14 Days)

At this point, within the study, it is expected that a large proportion of participants will reside in the community. Therefore, participants are to receive study follow-up via either telephone or face-to-face appointment [21]. Telephone appointments should be scheduled with the participant to complete the patient-reported aspect of CRF B via the telephone. Follow-up appointments should be arranged to fall within the 90 days (± 14 days) poststoke window of opportunity, and a maximum of three attempts should be made to contact the participant. In circumstances where three unsuccessful attempts have been made to contact the participant or if the window of opportunity has elapsed, then the participant is to be considered lost to follow-up.

Face-to-face appointments can be used by research sites as a first preference. Participants with either or both communication difficulties and prestroke or poststroke cognitive impairment should be offered the option of either face-to-face or telephone appointments. The face-to-face follow-up appointments should be conducted in accordance with procedures outlined in Period A (≤14 days poststroke) data collection.

If participants are yet to be discharged from the hospital by 90 days (± 14 days) poststroke or have been rehospitalized, for reasons other than further stroke, then participants can also be followed up with CRF B but in line with procedures outlined in Period A (≤14 days poststroke) data collection.

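### The plan expects negligible missing outcome data but assumes 30% dropout at 6 months, and leaves any adjustment for that dropout optional

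*Protocol article*

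**What the plan says.** All references are to the protocol article.

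- **Primary outcome and precision.** The Conclusions paragraph of the Abstract states: "The primary outcome is the prevalence of morbidity at 6 months secondary to a stroke". The Data Analysis section sets a 95% CI of ±5 points as the target.
- **Sample size.** The Sample Size section states: "assuming a 35% morbidity rate, with a 95% CI width of ±5%, will require 350 stroke survivors". It continues: "Assuming that there is a 30% dropout [11] at the 6-month visit, the aim is to recruit a minimum of 500 stroke survivors".
- **Missing data.** The Missing Outcome Data section states: "we anticipate negligible missing instrument levels, and in this case, a complete case analysis will be carried out". Its next sentence deals with missing outcome data above 5%. Patterns are then explored and imputation is allowed but not required, with the method to depend on how much is missing and why.
- **Analysis population.** Data Analysis states: "All participants recruited in the study will be included in the analysis population".
- **Sources of loss.** The section on 60 days poststroke withdraws participants who have a further stroke or become palliative, and the 150-day section repeats it. For cognitive noncompletion, including aphasia and confusion, the section on cognitive causes ends attempts at patient-reported data for that occasion. The section on physical or visual causes bars secondary sources for the cognitive screen, the PROM and the mood screen, but allows them for sequelae and function.
- **Failed contact at day 90.** After three failed attempts, or once the window has passed, the Period B section says "then the participant is to be considered lost to follow-up".

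**The concern.** The two expectations cannot both describe the 6-month outcome. A study that recruits 500 in order to keep 350 does not expect 5% or less missing. The complete-case statement is therefore written for a situation that the plan does not expect, while the situation it does expect has only an optional remedy.

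This matters because the main result is a single prevalence in one cohort. No between-group comparison exists in which selection might partly cancel. Recruiting more people to offset dropout protects the width of the CI but does nothing about bias, and a complete-case CI reflects sampling error alone.

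The document gives reasons to expect loss related to outcome. Aims and Objectives counts aphasia, cognitive impairment, anxiety and depression as morbidity. The noncompletion rules mean that some people with those conditions will have no result on the instruments meant to detect them.

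**Working it through.** **1. Reproduce the sample size.** Inputs from Sample Size: p = 0.35, half-width d = 0.05, dropout 30%.

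- n = 1.96² × 0.35 × 0.65 / 0.05² = 349.6, so 350.
- 350 / (1 − 0.30) = 500.

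Both figures agree with the document, so the design does build in a 30% loss.

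**2. Compare with the 5% limit.** Planned loss is 500 − 350 = 150, and 150/500 = 30%. Then 30/5 = 6 times the limit in Missing Outcome Data. The complete-case condition fails and the rule for more than 5% applies.

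**3. What that rule requires.** It requires patterns to be explored. It does not require adjustment, name a primary method or call for a sensitivity analysis. An analyst who explored patterns and then reported complete case would have complied.

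**4. Illustrative bias.** Let q be the prevalence in the unseen 30%. The documents do not give q, so it is shown as a range, with every unseen participant taken as a survivor.

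- True prevalence = 0.70 × 0.35 + 0.30 × q
- Bias = 0.35 − true prevalence = −0.30 × (q − 0.35)
- SE = √(0.35 × 0.65 / 350) = 2.55 points
- Coverage = Φ(1.96 − |bias|/SE) − Φ(−1.96 − |bias|/SE)

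| q (assumed) | True prevalence | Complete-case bias | Coverage of nominal 95% CI |
|---|---|---|---|
| 25% | 32.0% | +3.0 points | about 78% |
| 35% | 35.0% | 0 | 95% |
| 40% | 36.5% | −1.5 points | about 91% |
| 45% | 38.0% | −3.0 points | about 78% |
| 50% | 39.5% | −4.5 points | about 58% |
| 60% | 42.5% | −7.5 points | about 16% |

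The bias equals the whole ±5-point target when q = 0.35 + 0.05/0.30 = 51.7%, about 52%.

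**5. Bounds without any assumption about q.** With 30% missing: 0.70 × 0.35 = 24.5% to 24.5% + 30% = 54.5%. With 5% missing: 0.95 × 0.35 = 33.3% to 33.3% + 5% = 38.3%. A 5% limit keeps the possible error small; a 30% loss does not.

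**6. Effect of deaths.** If k of the 150 have died, the missing fraction among survivors is (150 − k)/(500 − k). This is below 30% for any k above 0. The bias for survivors is that fraction times (0.35 − q), so steps 4 and 5 are upper limits on its size at each q. The documents do not say whether the 30% includes deaths.

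**The case against.** **The plan does not prescribe complete case at 30% loss.** A reader who stops at the complete-case sentence might infer that the primary prevalence will rest on an unadjusted, selected 70%. The next sentence prevents that reading, because above 5% the plan moves to exploration and possible imputation. This objection stands, and the criticism is confined to what the rule permits.

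**The 5% and the 30% may be different quantities.** The expectation of little missing data is worded in terms of instruments and credited to the data collection methods. It could mean incomplete forms among people who were assessed. This has some force. But the section is headed for missing outcome data, the following sentence applies the 5% limit to outcome data in general, and the article gives no other rule for dropout. On the narrower reading, 30% dropout has no stated handling at all. Either way the text needs reconciling.

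**Including all recruited participants does not conflict with complete case.** This is right. A population definition and a missing-data rule are separate things. Someone without a 6-month value can still contribute baseline and Period B data, for example to the multilevel model under Morbidity Prediction.

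**Imputing outcomes for the dead.** A reader might infer this from the all-recruited population. Nothing in the document says so: the method depends on the reason for missingness, vital status is checked at days 60 and 150, and the sample size refers to survivors.

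**Period B non-contact need not end follow-up.** The document does not say that such a participant is withdrawn, and the 150-day and Period C sections exclude nobody for missing Period B. The wording is ambiguous, not a stated loss of day-180 data.

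**Method detail belongs in an analysis plan.** The full protocol or analysis plan may name a method, and its absence from an article is no finding. The point rests on what the article does state: an expectation that its own sample size contradicts.

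**Conclusion.** The point holds in a limited form. Missing Outcome Data anticipates 5% or less missing, while Sample Size plans for 30% at the primary time point. The rule that would then apply leaves adjustment optional, so an unadjusted prevalence in about 350 of 500 would comply with the plan.

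Outcome-related loss is plausible from the withdrawal and noncompletion rules. It is limited by the permission to use secondary sources for sequelae and function. The documents give neither its size nor its direction. The range of −1.5 to −7.5 points rests on an assumed 40% to 60% morbidity in the unseen, 35% in the seen, and no deaths among the missing. It shows that the error could match or exceed the ±5-point target. It does not show that it will.

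**What to change.** 1. **Reconcile Sample Size and Missing Outcome Data.** Limit the statement on negligible missingness and complete case to items missing among participants who were assessed.
2. **Commit to a method for missed 6-month visits.** Make the primary estimate multiple imputation or inverse-probability-of-response weighting in participants alive at 6 months. Use variables already collected, such as age, sex, stroke type, prestroke mRS, baseline RFA, SF-MoCA, PHQ-4, consultee status, site and Period B values. Add a delta-adjusted sensitivity analysis, give complete case as secondary, and report deaths separately.
3. **Clarify the Period B section.** State that failed contact at day 90 is a missed visit and that Period C is still attempted.

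The cost is a revision of the analysis wording, modest extra analysis, one line to sites and a slightly less simple headline estimate. No sample-size figure changes and no new data are needed. According to Results, analysis starts only after all data are in, so items 1 and 2 can be settled beforehand. Item 3 helps only while follow-up is still running.
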